**Title: The smart-phone as a physical fitness monitor on a population level – validity and sensitivity**

**BACKGROUND**

Low physical fitness is an independent predictor of a range of non-communicable diseases including Type 2 Diabetes (T2D) and all-cause mortality [1-3]. In addition, peak oxygen consumption ( $VO_{2peak}$ ) is the most validated marker of cardiopulmonary exercise capacity, which is used in daily clinic for investigating cardiac and pulmonary disorders [4, 5]. Valid continuous monitoring of  $VO_{2peak}$  would thus be of clinical and scientific importance.

To improve  $VO_{2peak}$  and physical activity in T2D patients we recently examined the feasibility of implementing Interval walking (IWT) and continuous walking training in a sample of T2D patients in a four-month trial [6]. A small tri-axial accelerometer training device (JD Mate; Kissei Comtec, Matsumoto, Japan) was employed to initiate and monitor exercise. IWT, but not continuous walking, resulted in remarkably beneficial effects on physical fitness level (16%). Moreover, this was achieved with a compliance rate of ~90% and low drop-out. Thus the exercise modality and the device employing it seem very feasible. The device individualizes exercise intensity by using the onboard accelerometer to estimate  $VO_{2peak}$ . This has been validated in an elderly Japanese sample [7], but it remains unknown to what extent estimated  $VO_{2peak}$  is sensitive to exercise adaptation, therefore unknown if it can be used in clinic and interventional research. Due to the large costs (2.500 Danish kr.) and lack of stability of the training device, implementation of IWT and the fitness test in clinic and in larger samples is difficult and expensive. Therefore, we developed the free InterWalk smart-phone application as an interventional tool for the 'Danish Centre for Strategic Research in Type 2 Diabetes' (DD2). Briefly, the DD2 aims is to prevent co-morbidities and to ensure normal quality of life and life expectancy in newly diagnosed T2D patients through range of strategies, among these are increases in exercise and physical activity [8].

The application is a free personal trainer individualizing IWT by employing the on-board accelerometer and global positioning system (GPS) to specify walking intensity and speed. Intensities are determined, as with the accelerometer-based training device with the option of including GPS determined walking speed. Data from the fitness test is logged on a server, and as the CPR-number is a part of the profile information on the application, it will enable researchers and clinicians to combine it with health information using the Danish registers. However, the validity of the  $VO_{2peak}$  test functions and sensitivity to exercise adaptation of smart-phone based tests are at large, unknown. As the DD2 are establishing a large cohort consisting of ~50.000 newly diagnosed T2D patients, a valid tool for assessing exercise capacity on a large scale is needed [8]. Moreover, if valid, this application provides clinicians and researchers with an easy and cheap tool to estimate physical fitness in clinic and in very large samples and not only in T2D patients.

The  $VO_{2peak}$  test is conducted by the patients using their smart-phones and it is based on three self-selected walking paces - slow, moderate and high. It is uncertain to which extent the self-selected walking paces are adequate to reflect a  $VO_{2peak}$ . Furthermore, as T2D patients have limited experience with exercise training, we speculate that acclimatization to high intense walking and pacing during the  $VO_{2peak}$  test can improve the validity.

The aim of the study is to validate the ability of the smart-phone based IWT application to accurately reflect physical fitness in a sample of T2D patients. More specifically we aim to;

- 1) Develop an algorithm for conversion of the  $VO_{2peak}$  test output to energy expenditure and validate the algorithm against maximal oxygen consumption in an independent sample. We hypothesize that the  $VO_{2peak}$  test algorithm will be a valid measure of physical fitness if the peak test is performed at a sufficient walking pace.
- 2) Investigate the effect of acclimatization to high speed walking on the ability of the patient to perform a valid  $VO_{2peak}$  test. We hypothesize that acclimatization will increase walking economy in

the patients thus increase the walking pace during the  $VO_{2peak}$  test without any increase in physical fitness.

- 3) To investigate sensitivity of the  $VO_{2peak}$  test function to reflect actual changes in the maximal oxygen consumption. We hypothesize that a three-month IWT intervention will improve the maximal oxygen consumption and the improvement will be reflected in the  $VO_{2peak}$  test.

## STUDY DESIGN

**Subjects, screening and sample size:** A total of  $n=50$  TD2 patients will be included in the study. All patients will undergo the protocol and intervention. However, 25 persons will be randomly chosen to act as a cross-validation reference group. Their data will act as reference to the developed algorithm. Based on previous studies on the association between  $VO_{2peak}$  and the maximal oxygen consumption ( $VO_{2max}$ ) we expect a correlation of 0.7. With a power of 0.8 ( $1-\beta$ ) and  $\alpha$  set at 0.05, allowing for four covariates we need a least 23 subjects undergo the study (group 1). With an *a priori* difference of 0.1 between the correlation coefficient ( $\rho^2$ ) in group 1 and the correlation coefficient in the independent sample (group 2) ( $\omega^2$ ), allowing for four covariates with we need 25 subjects in the cross-validation sample [9]. A medical examination, standard anthropometric measures, medical history, blood chemistry screen, ECG, oral glucose tolerance test (OGTT), Dual x-ray absorptiometry (DXA) scan, an assessment of walking economy, assessment of resting energy expenditure (REE), a smart-phone based  $VO_{2peak}$  test and a laboratory  $VO_{2max}$  test will be performed. If an individual meets the inclusion criteria, informed oral and written consent will be obtained prior to participation in the study, in accordance with guidelines developed by the ethical committees. For participants without a smart-phone the exercise and  $VO_{2peak}$  tests will administered on an iPod Touch.

**Inclusion Criterias:** T2D, age 30-70 y, BMI >18 but <40 kg/m^2 and confirmed T2D diagnose.

**Exclusion Criterias:** Pregnancy, smoking, contraindication to increased levels of physical activity [10], insulin dependence, evidence of thyroid, liver, lung, heart or kidney disease

**Recruitment, information and informed consent:** Potential subjects are recruited through advertising on "www.forsogsperson.dk" and advertising in local health care centers. Potential subjects contact one of the project participants by telephone and are orally informed about the study. If no exclusion criteria are identified through the telephone interview, the written material and consent form is mailed to the participant with a free post envelope and he/she will be encouraged to read the information thoroughly. The potential participant is furthermore offered an information meeting, and the potential subject is informed about the possibility of inviting a private counselor to the information meeting. If the information meeting is requested, the study information will be given in a closed room where only the scientific participant, the potential subject and the potential private counselor will be present. If the potential subject is ready and wants to participate in the study, the study participant will be required to mail the informed consent form no earlier than 24 hours after the meeting. If the potential subject wants additional time to consider whether or not to participate in the study, an agreement about a telephone meeting after approx. one week is made. The subject will be informed of the possibility of contacting one of the scientific participants by telephone, in case of questions. If no additional oral information, besides the information provided initially by phone, is needed, the possible participant can return the consent form no earlier than 24 hours upon reception of the written material. Upon reception of the consent form by the scientific staff, the subject will be contacted by a member of the scientific staff and a date for the first visit is arranged.

**Study design:** The study is a validation study where the primary endpoint is  $VO_{2peak}$  and indirect calorimetry is used as reference to assess face validity of the InterWalk test. Data from all the study participants will serve a material for development of algorithms to predict  $VO_{2peak}$ . Data from the first and second lab day will form basis for a cross validation. Data from the third lab day will serve as material to

detect the sensibility in changes in  $VO_{2peak}$ . Throughout the study period all participants will use the InterWalk application to engage in interval walking training (exposure) [6]. To assess convergent validity and to confirm diabetes status an OGTT is employed. Study participants will complete a variety of tests across three laboratory days, over a period of three months. Table 1 describes the sequence of the tests included in the study. The study timeline is depicted in Figure 1. Participants will be instructed to fast, refrain from smoking and physical activity for 9 hours prior to the tests. After the assessment or REE or the OGTT the participants will be offered a meal.

[figure not shown]

Figure 1: Study timeline

| Table 1 Measurements included in the study                        |                                                       |                           |
|-------------------------------------------------------------------|-------------------------------------------------------|---------------------------|
| Day 1                                                             | Day 2                                                 | Day 3                     |
| Medical examination                                               | REE                                                   | As day 2                  |
| Assessment of resting energy expenditure (REE)                    | 2-hour Oral glucose tolerance test (OGTT)             | A graded $VO_{2max}$ test |
| Anthropometric measures                                           | DXA scan                                              |                           |
| Self-administered free living smart-phone based $VO_{2peak}$ test | Self-administered Smart-phone based $VO_{2peak}$ test |                           |
| Paced free-living smart-phone based $VO_{2peak}$ test             | Paced smart-phone based $VO_{2peak}$ test             |                           |
| Assessment of walking-economy                                     | Assessment of walking-economy                         |                           |
| A graded $VO_{2max}$ test                                         |                                                       |                           |

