## FEASIBILITY

In collaboration with the DD2 IWT committee ([name] [name], [name], and Professor, chief clinician [name]. fellow [name], Post. Doc. [name] and DD2 project coordinator [name]) I have designed the protocol and results from the study will be implemented in the DD2. I have previously conducted validation studies on measurements of free-living physical activity and am an expert in measurements of physical fitness and metabolic monitoring [13-16]. The study is conducted in close collaboration with [name] who is an expert in the techniques necessary to complete glucose tolerance tests and DXA.

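### The random 25/25 split is inefficient internal validation, and the protocol contradicts itself on whether the algorithm is developed on 25 patients or on all 50

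*Protocol*

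**What the plan says.** In the protocol's STUDY DESIGN section, the paragraph on subjects, screening and sample size plans 50 patients who all follow the same protocol and intervention. It then says "However, 25 persons will be randomly chosen to act as a cross-validation reference group" and "Their data will act as reference to the developed algorithm". The two halves are sized separately. At least 23 are required for group 1, because "we expect a correlation of 0.7". For group 2, 25 are required, from an assumed "difference of 0.1 between the correlation coefficient" of the development group and that of the independent sample. Both calculations allow for four covariates.

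Aim 1 (BACKGROUND) and STATISTICAL ANALYSES both say that the algorithm is validated in an independent sample, the latter by Bland-Altman plots. The algorithm comes from backward stepwise linear regression with age, height, gender and monitor placement as covariates.

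The later paragraph headed Study design says something different: data from every participant are to be used to develop the prediction algorithms.

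On use, FEASIBILITY says that "results from the study will be implemented in the DD2". BACKGROUND describes the DD2 as a cohort of about 50,000 newly diagnosed patients.

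**The concern.** The sample-size paragraph and the Study design paragraph cannot both be followed with the held-out 25 remaining independent. Each reading has a cost.

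- **The split governs.** The equation uses half the data and its validity is judged on the other half. The hold-out is a random half of one cohort with common recruitment, measurements and training, so it tests no new population. It is internal validation with half the patients removed from each task, and the answer depends on which 25 are drawn.
- **All participants develop the algorithm.** The equation uses the data well, but the reference patients helped to build it. Agreement in those 25 would look better than it is, and this document describes no other check of the 50-patient equation.

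At stake are the accuracy of an equation meant to inform work in a large cohort, and the precision of the statement about how valid it is.

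**Working it through.** **Inputs.** From the sample-size paragraph: N = 50, 25 held out, r = 0.7 (so R² = 0.49), power 0.80, α = 0.05, four covariates, tolerated loss ρ² − ω² = 0.1. From STATISTICAL ANALYSES: app output plus four covariates, one of them placement, which has three sites (METHODS). That gives 5 slopes, or 6 if placement takes two; 4 is the count in the sample-size text. Assumed: normal independent predictors, one record per patient, no dropout.

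**1. The plan's own figures.** For group 1, f² = 0.49/0.51 = 0.961. The overall F test with noncentrality f²(N − k − 1) needs 22 patients (k = 4) or 24 (k = 5), so 23 is reproduced within that bracket. Noncentrality f²N gives 18 or 20, and random regressors give 20 or 22. For group 2, 25 is reproduced if 0.7 is read as the *squared* correlation: with 4 predictors, 25 patients give probability 0.90 that ρ² − ω² ≤ 0.1. With ρ² = 0.49, probability 0.80 needs 28 patients (4 predictors) or 35 (5). In this check the loss depends on the sample that *derives* the equation.

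**2. Accuracy of the equation.** For least squares with p normal predictors, expected prediction error variance divided by residual variance is (n + 1)(n − 2) / [n(n − p − 2)].

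| p | n = 25 | n = 50 | RMSE reduction |
|---|---|---|---|
| 4 | 598/475 = 1.259 | 2448/2200 = 1.113 | 1 − √(1.113/1.259) = 6.0% |
| 5 | 598/450 = 1.329 | 2448/2150 = 1.139 | 7.4% |
| 6 | 598/425 = 1.407 | 2448/2100 = 1.166 | 9.0% |

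R² cancels from these ratios. With backward selection (5 candidates, 150 simulated trials) RMSE is 0.841 against 0.787, a reduction of 6.4%. Across the simulated scenarios the 50-patient equation was the better one in 83–90% of trials.

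**3. The protocol's 0.1 tolerance.** Simulated chance that ρ² − ω² ≤ 0.1, with ρ² = 0.49:

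| p | fitted on 25 | fitted on 50 |
|---|---|---|
| 4 | 77% | 96–97% |
| 5 | 64–65% | 93–94% |
| 6 | 51–53% | 88–89% |

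Ranges show the spread between separate simulations. If 0.7 is instead a squared correlation, the chances at 25 are 91% (p = 4) and 83% (p = 5), and above 99% at 50.

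**4. Precision of the validity estimate.** Each method's RMSE for the true validity correlation of its own equation, over simulated trials of 50 patients with R² = 0.49:

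| Scenario | 25/25 split | Repeated 10-fold CV | Bootstrap |
|---|---|---|---|
| 4 slopes | 0.130 | 0.106 (−18%) | 0.085 (−35%) |
| 5 slopes | 0.130 | 0.107 (−18%) | 0.087 (−33%) |
| 5, backward selection | 0.126 | 0.114 (−10%) | 0.084 (−33%) |

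With R² = 0.7 and 5 slopes the errors are 0.079, 0.055 and 0.045. The estimated size of prediction error, on which limits of agreement rest, also improves at R² = 0.49: its RMSE falls from 0.116–0.123 to 0.082–0.090 (SD of VO2max = 1). Cross-validation ran low, understating r by 0.036–0.040 at R² = 0.49. The bootstrap ran high by 0.022 under backward selection, in a run that used only 20 bootstrap samples.

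**The case against.** The strongest reply is that the split is deliberate. The protocol commits to an independent check, sizes both groups for it and cites a cross-validation sample-size method. An equation refitted on all 50 would never meet patients outside its own development. That stands, and it is why the hold-out should be kept. It does not make a random half of one cohort an external sample.

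A second reply is that refitting before release is often settled in an SAP, which is not shown. That also stands, so the absence of a refit is not itself the finding. The finding rests on what the protocol does fix: the single split, and the conflict over who develops the algorithm.

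Four stronger readings are tempting and are not supported.

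- *The DD2 equation is certainly fitted on half the patients.* The Study design paragraph says otherwise, and FEASIBILITY speaks only of results being implemented.
- *Limits of agreement would narrow by 9%.* That is the six-slope case. All three phones are worn at once (METHODS), so placement varies within patients and may cost less than two between-patient slopes. With 4 or 5 slopes the gain is 6–7%.
- *The validity interval shrinks as if 50 new patients were tested.* A Fisher interval for r = 0.7 is 0.42–0.86 at n = 25 and 0.52–0.82 at n = 50, but resampled patients also fit the model. Step 4 gives the fairer measure.
- *The plan cannot tell a good phone test from a poor one.* The protocol sets no threshold for either, and the interval at 50 is also wide.

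Finally, the calorimetry runs through several test stages and days, so one record per patient at R² = 0.49 simplifies the real data. The sizes are therefore indicative.

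**Conclusion.** The concern holds in this form: the statements on the split, on independence and on whose data develop the algorithm conflict and must be reconciled, and neither reading uses the 50 patients well. Under the split, the loss is modest for the equation (about 6–9% in RMSE, 6–7% with 4 or 5 slopes). It is larger for the validity estimate, where error in the correlation could be cut by roughly 10–18% with repeated cross-validation or about a third with the bootstrap. At R² = 0.49 a 25-patient fit meets the protocol's own 0.1 tolerance only about 51–77% of the time, against 88–97% for 50. That last comparison weakens if 0.7 was meant as a squared correlation. Under the all-participants reading the equation loses nothing, but its validation is not honest.

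This is a worthwhile, cheap improvement rather than a flaw that invalidates the study. The direction was the same in every scenario run; the sizes rest on the assumptions listed with the inputs.

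**What to change.** 1. Reconcile the sample-size paragraph, the Study design paragraph, aim 1 and STATISTICAL ANALYSES, so that they agree on which patients develop the algorithm and which test it.
2. Keep the 25-patient hold-out as a first check, with those patients fully excluded from the development of the equation tested on them.
3. Then refit the whole procedure, backward selection included, on all 50 to obtain the equation to be released.
4. Report that equation's optimism-corrected R², calibration slope and limits of agreement from a bootstrap that resamples participants. Repeat the selection in every bootstrap sample and keep all placements and test days of a patient together.
5. Describe this as internal validation.

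The cost is analysis work only, with no extra patients, visits or measurements. The small downside is that the released equation is validated by resampling rather than in a separate group.

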## STATISTICAL ANALYSES

Based on previous research it is assumed that the smartphone accelerometer output increases linearly until app. 9-10 km/h [12]. As it is not expected that our participant exceed this speed, backward stepwise *linear* regression analysis will be employed to develop an appropriate algorithm. In the full model we will include age, height, gender and monitor placement as co-variables. Log-likelihood test of the model fit will be employed to find the best fit to the data. Standard assumptions, such as linearity, independence between co-variables and normality of residuals will be checked. Bland-Altman blots will be used to assess the validity of the algorithm in an independent sample.

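### The Study design paragraph develops the algorithm on all participants, although 25 of them are set aside elsewhere as the independent validation group

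*Protocol*

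**What the plan says.** The protocol describes the use of the participants in four places.

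- **Subjects, screening and sample size:** "A total of $n=50$ TD2 patients will be included in the study". Of these, "25 persons will be randomly chosen to act as a cross-validation reference group", and "Their data will act as reference to the developed algorithm". The paragraph sizes two groups separately: at least 23 for group 1 and 25 for group 2, which it calls the independent sample.
- **Background, Aim 1:** the intention is to "validate the algorithm against maximal oxygen consumption in an independent sample".
- **Statistical Analyses:** backward stepwise linear regression builds the algorithm, and then "Bland-Altman blots will be used to assess the validity of the algorithm in an independent sample".
- **Study design:** "Data from all the study participants will serve a material for development of algorithms to predict" VO2peak. The next sentence adds: "Data from the first and second lab day will form basis for a cross validation".

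The first three describe a split by person. The fourth describes development on everyone, with cross-validation tied to visits.

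**The concern.** All participants include the 25 reference participants. No sentence excludes those 25 from development, and no outside cohort is planned. Under the Study design wording, the same 25 people would help to choose the predictors and estimate the coefficients, and would then be used to judge the result. Their r² and limits of agreement would be partly re-substitution figures.

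The lab-day sentence does not restore independence. Fitting on one day and testing on another within the same people still lets each person contribute to both sides.

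What is at stake is the main result of a validation study: the claim that the phone test reflects measured fitness in people who did not shape the equation. An analyst could follow either rule, and could do so after seeing which gives the better agreement. This is not a detail left open for a statistical analysis plan. The protocol states two incompatible rules.

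**Working it through.** **1. Inputs from the protocol.** Total 50; reference group 25; expected correlation 0.7, so ρ² = 0.7² = 0.49; power 0.8; α 0.05; four covariates; a priori difference 0.1 between ρ² and ω². The full model has age, height, gender and monitor placement plus the accelerometer output, which gives 4 to 6 terms depending on what is counted and how placement is coded.

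**2. The plan's own sample sizes.**
- *Group 1 (23).* Overall F test of R² = 0.49, with f² = 0.49/0.51 = 0.961 and noncentrality f²(n − p − 1). The smallest n with power 0.8 is 22 for p = 4 and 24 for p = 5. At n = 23 and p = 4, power is 0.85. The stated 23 is reasonable.
- *Group 2 (25).* Smallest n for which ρ² minus the cross-validity is at most 0.1, by simulation. If this must hold on average at ρ² = 0.49, n is 19 (p = 4) or 24 (p = 5). If it must hold with 80% probability, n is 28 or 34. The protocol does not say which criterion gave 25, but the figure lies among these variants.

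Both sizes fit a 25/25 split by person.

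**3. What overlap does to the result.** The protocol gives no figure for this, so it was simulated. Assumptions: normal predictors, ordinary least squares, full model without selection, one record per person, ρ² = 0.49. The equation is scored in 25 people under three arrangements. Entries are mean squared correlations.

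| Predictors | (a) Fit on 50, scored on 25 of them | (b) Fit on 50, scored on 25 new people | (c) Fit on 25, scored on the other 25 | a − b | a − c |
|---|---|---|---|---|---|
| 4 | 0.522 | 0.460 | 0.424 | 0.062 | 0.098 |
| 5 | 0.534 | 0.449 | 0.404 | 0.085 | 0.130 |
| 6 | 0.544 | 0.439 | 0.383 | 0.105 | 0.161 |

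Column a − b is the optimism of the 50-person equation itself. Column a − c is the gap from the planned split; it also reflects the poorer equation obtained from 25 people.

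**4. Bland-Altman scale.** SD of the differences, in units of the residual SD, for (a) against (b):
- 4 predictors: 0.948/1.034 = 0.917, about 8% too narrow
- 5 predictors: 0.937/1.045 = 0.897, about 10%
- 6 predictors: 0.926/1.057 = 0.876, about 12%

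**5. Sensitivity.**
- *If 0.7 is read as R² rather than r* (full model, 4 to 6 predictors): a − b is 0.038 to 0.065, and a − c is 0.063 to 0.109.
- *With backward elimination by likelihood-ratio test at the 5% level, ρ² = 0.49, only the accelerometer term mattering:* a − b is 0.022 (4 terms) to 0.035 (5 terms), and a − c is 0.034 to 0.044.
- *With the same elimination and all five terms mattering:* a − b is 0.107 and a − c is 0.204.

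Over these settings the r² inflation runs from about 0.02 to 0.20. It is upward in every one.

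**The case against.** The strongest reply is that one loosely worded sentence should not outweigh the rest. Aim 1, the sample-size paragraph and the Statistical Analyses section agree on an independent sample, and the two separately sized groups make sense only with a split. The Study design sentence may be a loose summary of development plus validation, or may mean a final refit on pooled data. This stands in part: the bias is conditional on the literal reading, and under the sample-size paragraph there is none. But neither milder meaning is written, and the lab-day sentence that follows points away from a split by person.

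A reader might infer that the validation will be optimistic by the plan's own 0.1 margin. The documents do not support that. Their 0.1 is an allowance for ρ² minus ω², that is, shrinkage, used to size group 2. It is not apparent minus true r². In the full-model simulation, shrinkage with 50 development participants is 0.49 − 0.457 = 0.033 (4 predictors) to 0.49 − 0.435 = 0.055 (6 predictors), about a third to a half of 0.1. The optimism is a different quantity and moves widely with the assumptions.

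Two further limits are fair. The named validity analysis is Bland-Altman, where the full-model effect is real but moderate. And each participant wears three phones, so the real data are repeated records, which the simulation simplifies to one per person.

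A reader might also infer that the split ought to be abandoned for resampling. The contradiction does not require that. It is a design trade-off, and the protocol has sized and promised a hold-out.

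**Conclusion.** The contradiction stands in the current text. The Study design paragraph cannot be followed together with the 25-person reference group and the independent sample promised in Aim 1 and the Statistical Analyses section. Followed literally, it leaves no independent sample and makes the main validity result optimistic.

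The magnitudes depend on assumptions and are not stated by the protocol. The central case (ρ² = 0.49, full model, 4 to 6 predictors, one record per person, compared with the same equation in new people) is the one in steps 3 and 4 of the working; the wider range in step 5 shows how little the exact size can be relied on. The direction is the firm part. Because the rule governs the primary aim and cannot be settled credibly once results are known, it should be settled before the algorithm is fitted.

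**What to change.** Reword the Study design paragraph to state one rule:

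1. Estimation and backward selection use only the 25 participants not chosen for the reference group.
2. The split is by person and covers all lab days and all phone placements, so that no one contributes records to both sides.
3. The equation is locked, then applied once to the 25 reference participants.
4. The lab-day sentence is restated to say which visits' data are used within that split, not as a separate form of cross-validation.

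If the sponsor prefers to develop on all 50, the hold-out and independent-sample wording must be replaced throughout by person-level bootstrap or cross-validation that repeats the selection step in every resample, labelled internal validation. In the full-model simulation this gives a somewhat better equation (6 predictors: 0.439 in new people from 50, against 0.383 from 25), at the price of giving up the promised independent sample.

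Either route costs a few sentences; the second also needs a resampling program. Neither needs more participants or measurements. Compared with the literal reading, the reported validity will probably look less favourable.
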